## Sample size and study population

The fundamental rationale relies on the limited capacity theory of attention, positing that highly immersive multisensory environments exhaust finite cognitive resources to mitigate acute pain perception [7]. Furthermore, as demonstrated by Lier et al., virtual reality yields significant overall analgesic efficacy (SMD = −0.65), with particularly robust effects observed among younger demographics [8]. Consequently, the trial enrollment focuses on 60 patients aged 16 to 40 years. Eligible procedures include cardiac and specific thoracic surgeries, such as pulmonary decortication, video-assisted thoracoscopic surgery (VATS), lung biopsy, and Nuss bar pectus excavatum repair.

As this trial is designed as an early-stage, proof-of-concept efficacy study in the specific context of cardiac surgery, a formal a priori power calculation for clinical efficacy is not performed. Instead, a pragmatic sample size of 20 patients per arm (total N = 60) is established. This sample size is aligned with phase IIa / proof-of-concept trials aimed at detecting large clinical effect sizes, evaluating the safety profile of the intervention, and providing initial estimates of variance (mean and standard deviation) to adequately power future, large-scale definitive multicenter trials.

While previous studies have demonstrated substantial effect sizes for VR analgesia in other surgical contexts, extrapolating those parameters to a three-arm, highly invasive cardiothoracic population is not methodologically sound for an a priori power calculation. Therefore, this sample size of 60 serves as a pragmatic and methodologically sound approach. It is sufficiently large to evaluate our primary feasibility metrics and safety profiles, while providing exploratory signals regarding the cumulative opioid consumption to inform future research.

The inclusion criteria encompass patients aged 16 to 40 years, a demographic targeted as meta-analyses confirm that younger individuals exhibit significantly greater analgesic efficacy from virtual reality interventions [8]. Eligible surgical procedures comprise specific cardiac interventions, including valve surgery, myocardial revascularization, aortic procedures, and congenital heart defect corrections [9], alongside thoracic operations, namely pulmonary decortication, video-assisted thoracoscopic surgery (VATS) [10], lung biopsy, and Nuss bar pectus excavatum repair. The aggregated analysis of these major cardiothoracic procedures is scientifically justified by their shared pathophysiological pathways and homogeneous moderate-to-high postoperative pain intensity, which is consistently exacerbated by surgical chest wall trauma, inherent to both sternotomies [11] and thoracoscopic ports [12], as well as the nociceptive stimulus of thoracic drains [13]. Furthermore, because pain perception is fundamentally constructed by a central neural network independently of the specific peripheral incision [14], virtual reality effectively acts as an immersive cognitive distractor that attenuates pain-related cortical processing; thus, its therapeutic efficacy remains robust and comparable across distinct surgical traumas [15]. This unified approach is further supported by prospective evidence demonstrating that the incidence and intensity of acute postoperative pain do not significantly differ between patients undergoing median sternotomy and those undergoing thoracic incisions [16]. Finally, a preoperative Mini-Mental State Examination (MMSE) score of 25 or higher remains a mandatory inclusion criterion for all three study arms. By enforcing this universal cognitive threshold, the study ensures that participants in both the intervention and control groups possess the necessary cognitive capacity for effective interaction with immersive virtual reality environments [17], reliable participation in pain assessment protocols, and a clear understanding of the study instructions.

Conversely, the exclusion criteria are systematically applied and scientifically justified to ensure patient safety and protocol fidelity:•**Clinical and Operational Status:** Patients currently requiring invasive mechanical ventilation at the time of the scheduled intervention (due to physical interference with the VR headset and inability to interact), or those presenting with active infectious-contagious diseases. Recent surgical trials dictate that these exclusions are critical, as such clinical states limit the required active cooperation, pose risks of device displacement, and significantly increase the likelihood of cross-contamination with head-mounted displays [18].•**Cognitive and Neurological Baseline:** Patients with a documented cognitive deficiency, defined by a Mini-Mental State Examination (MMSE) score of 24 or lower, as well as those diagnosed with other cognitive disorders or spatial orientation deficiency. This specific cutoff is supported by Cochrane systematic reviews, which demonstrate that an MMSE score of 24 provides an optimal balance of 85% sensitivity and 90% specificity for detecting cognitive impairment, thereby preventing the inclusion of individuals unable to fully comprehend instructions or interact with complex virtual environments [19].•**Physical and Sensory Constraints:** Individuals with sensory or physical limitations, specifically severe visual impairments and upper limb motor deficits. This exclusion guarantees that patients possess the physical ability to safely interact with the hardware and fully perceive the virtual environment.•**Psychological and Vestibular Intolerance:** Conditions that directly contraindicate immersive technologies, notably claustrophobia and motion sickness, including labyrinthine diseases. While recent meta-analyses confirm that virtual reality is generally safe, mild adverse events such as nausea, dizziness, and cybersickness are still reported, with some clinical trials noting dropout rates of up to 13% due to these symptoms, making the exclusion of highly susceptible populations essential to guarantee patient safety and maintain strict protocol adherence [20].

## Virtual reality interventions

For the intervention arms, a progressive additive model is applied to ensure clear methodological differentiation. Group 3 serves as the control and receives the institutional standard multimodal anesthesia and analgesia protocol. To maintain high external validity and reflect real-world intensive care conditions, pharmacological management and rescue analgesia for all groups are strictly governed by the institutional Standard Operating Procedure for Acute Pain Management. According to this protocol, pain is objectively assessed during every routine vital sign check. Adequate pain control is institutionally defined as a Visual Analogue Scale (VAS) score of 3 or less. Consequently, subjective bedside dosing is minimized, as any reported pain score of VAS ≥ 4 (categorized as moderate to severe pain) triggers mandatory re-evaluation and the administration of standardized rescue interventions—including oral, intermittent intravenous, or PCA titrations—until the target of VAS < 3 is achieved. Furthermore, to preserve the pragmatic nature of the trial, participants in the control group are not restricted from using standard non-immersive personal devices, such as smartphones or hospital televisions. Restricting access to these devices is considered ethically and logistically inviable due to the essential need for family communication during a critical postoperative period and the inherent setup of shared hospital rooms. Therefore, this study is pragmatically designed to evaluate the supplementary efficacy of virtual reality immersion against the baseline noise and unstructured digital distractions that already constitute the real-world standard of care. This methodological allowance is further grounded in the premise that the therapeutic mechanism of virtual reality relies on multisensory immersion, which fundamentally differs from the limited cognitive engagement provided by conventional two-dimensional screens.

Regarding the experimental arms, Group 2, designated as the passive therapy arm, receives the identical standard clinical protocol supplemented with the Meta Quest VR headsets, providing access to the YouTube VR platform for passive immersion. Crucially, rather than restricting individuals to a standardized preselected playlist, the protocol allows the free selection of 360-degree videos, encompassing nature, space, or cultural events, based on individual preferences. This patient-centered design is methodologically grounded in the premise that cognitive distraction, which is the primary mechanism of action for pain modulation, is maximized when the visual stimulus aligns with the patient's intrinsic interests, thereby ensuring deeper emotional engagement.

Consequently, Group 1 represents the unrestricted enriched therapy arm, receiving the standard clinical protocol along with VR headsets equipped with both the passive YouTube VR content and immersive interactive gaming experiences. These active applications include Beat Saber, First Hand, Fruit Ninja 2, and Oculus First Contact, selected to ensure a diverse range of motor and cognitive engagement. By intentionally allowing free transition between active and passive content, this pragmatic design aims to evaluate whether providing the additional option of interactivity yields superior clinical outcomes and higher protocol adherence compared to the strictly passive device of Group 2. Rather than enforcing a rigid mechanistic isolation of active versus passive modalities—which could induce fatigue or jeopardize safety in acutely debilitated postoperative patients—this hybrid approach accommodates the fluctuating physical capacity inherent to intensive care recovery. Patients can safely initiate therapy with passive contemplation and progressively scale their physical and cognitive engagement as their clinical status improves. Under this framework, the primary intervention metric remains defined by the total duration of hardware exposure, reflecting the cumulative dose of immersive cognitive distraction driven by patient autonomy, regardless of the specific software application selected.

## Trial procedures and data collection

The protocol begins in the preoperative phase with a systematic cognitive screening applied to all potential participants. Specifically, the Mini-Mental State Examination (MMSE) is administered to every patient prior to surgery, including those subsequently randomized to the control group, to ensure a baseline of cognitive function that is homogeneous across the entire cohort. Furthermore, once clinically stabilized after surgery and extubated in the ICU, randomized patients start their assigned VR sessions from the first to the fifth postoperative day. The target duration for each session is 45 min to maximize the immersive analgesic effect. However, to prioritize patient comfort and mitigate visual fatigue, the protocol permits a voluntary early cessation at 30 min based on spontaneous patient requests, thereby defining the 30 to 45 min therapeutic window. These sessions are performed three times daily. The total cumulative time of hardware exposure is recorded for each participant to ensure a standardized evaluation of the immersive therapeutic dose across all intervention groups. Specifically, this therapeutic dose will be analyzed as a continuous variable, calculated by summing the total minutes across all 15 sessions. Early interruptions are not classified as protocol deviations, but rather as expected natural fluctuations in patient tolerance, being appropriately captured as a lower cumulative dose within the Intention-to-Treat (ITT) framework.

Researchers provide a training phase to ensure the patient is comfortable with the hardware and the virtual environment. Within this framework, the voluntary acceptance of the informed consent form serves as a natural filtration mechanism for technological affinity; by enrolling only participants who express interest and comfort with immersive digital activities, the study ensures a cohort predisposed to optimal therapeutic engagement, thereby mitigating potential variance related to prior gaming experience. Furthermore, to guarantee methodological consistency and eliminate behavioral bias, all research personnel undergo a standardized training program in accordance with Good Clinical Practice guidelines. The recruitment team, responsible for administering the informed consent form, is trained on the study rationale and experiences the virtual reality therapy to ensure standardized and neutral patient communication. Similarly, the bedside clinical team, tasked with conducting the sessions and collecting hemodynamic data, receives formal instruction emphasizing the critical importance of measurement accuracy. These professionals also complete hands-on simulation modules with the specific applications to assist patients with hardware operation. Finally, the data management team is trained on data extraction from both the institutional electronic health record system (Si3) and the bedside case report forms detailing the specific events of each therapeutic session. This rigorous training ensures the standardized transposition of all clinical variables into the REDCap platform, guaranteeing fidelity and traceability in data handling.

Data collection begins upon enrollment, encompassing demographic variables, biometric indices, and baseline clinical risk stratification. Specifically, the American Society of Anesthesiologists physical status classification will be assessed for the entire cohort, while the EuroSCORE II will be calculated for patients undergoing cardiac procedures. Preoperative cognitive function is quantified using the Mini Mental State Examination. Additionally, intraoperative parameters, including cardiopulmonary bypass duration, total anesthesia time, and intraoperative opioid titration, are recorded to account for potential confounding variables in the postoperative analgesic response. To ensure maximum data integrity and adherence to good clinical practice guidelines, all gathered clinical information will be securely entered and managed using the Research Electronic Data Capture (REDCap) electronic data capture tools hosted at the institution.

## Clinical endpoints and blinding

The primary clinical endpoint is defined as the cumulative morphine milligram equivalents consumed postoperatively, which is objectively quantified throughout the entire evaluation period. This fundamental outcome is monitored by tracking patient-controlled analgesia pump dosing logs to accurately record both requested and administered boluses. By assessing total opioid consumption within a pragmatic clinical framework, the study captures the intervention’s efficacy as an adjunct to routine postoperative analgesic management, accounting for the inherent clinical variability of an intensive care setting. Furthermore, due to the randomized design, it is assumed that exposure to institutional sedation protocols, chest physiotherapy, and intensive care environmental noise will be homogeneously distributed across all three arms, thereby neutralizing the influence of these confounding factors when comparing the intervention and control groups. To ensure accurate comparative analysis, all administered opioids, including rescue doses of medications such as tramadol, will be converted into cumulative morphine milligram equivalents according to standardized international pharmacological guidelines. Concurrently, the total daily consumption of non-opioid rescue analgesics, specifically dipyrone and paracetamol, will be independently calculated and recorded as the total cumulative daily dose in milligrams.

In parallel, as a crucial secondary clinical outcome, pain intensity is measured using the Visual Analogue Scale (VAS) at rest and during movement, which is specifically elicited by instructing the patient to take a deep breath. Evaluating dynamic pain represents the clinical gold standard, as joint practice guidelines from the American Pain Society and the American Society of Anesthesiologists emphasize that assessing pain during movement or activity is essential to accurately capture postoperative discomfort and guide functional recovery [21]. These VAS assessments are conducted at predefined and standardized time points throughout the day, ensuring temporal consistency across all three study arms. To clarify the Prospective Randomized Open, Blinded Endpoint (PROBE) design, we have explicitly defined the blinding status of all involved personnel. Due to the physical and highly visible nature of the Virtual Reality headsets, complete double-blinding is structurally impossible. Therefore, to mitigate detection and performance bias, a strict blinding matrix is established (Table 1).

**Table 1 tbl0001:** Blinding matrix for the PROBE design.

Role	Blinding Status	Justification / Mitigation Strategy
Participants	Unblinded	Inherent to the use of highly visible VR equipment.
VR Application Team	Unblinded	Researchers responsible for device setup and safety monitoring.
ICU Clinical Team	Unblinded	Cannot be blinded due to the shared, open ICU environment.
Pain Outcome Assessors	Blinded	Distinct staff exclusively assessing VAS. Patients are instructed daily not to discuss VR.
Statistician	Blinded	Data delivered with masked group codes (e.g., Group A, B, C).

By completely separating the personnel who administer the VR sessions from the clinical professionals who assess the Visual Analogue Scale (VAS) scores, the outcome assessors remain blinded to the assigned intervention. Additionally, the primary endpoint (cumulative opioid consumption) is quantified objectively via automated PCA pump logs and standardized medical records, structurally preventing expectancy bias from the outcome assessors.

Alongside these daily clinical assessments, the safety and tolerability of the intervention are continuously evaluated. Hemodynamic and respiratory parameters, comprising heart rate, mean arterial pressure, oxygen saturation, and respiratory rate, are recorded immediately before and after each virtual reality session. The research team actively monitors for signs of cybersickness, such as nausea or dizziness, as well as physical adverse events ranging from neck pain to skin lesions caused by the headset. Consequently, safety and hygiene protocols, which have been approved by the Hospital Infection Control Committee (CCIH), are paramount for trial replication. The equipment undergoes a cleaning process involving the disinfection of the headset's external hard plastic surfaces with 70 percent isopropyl alcohol wipes. To preserve structural integrity and prevent degradation of the anti-reflective coatings, the VR optical lenses and the auxiliary mirroring tablet screens are cleaned using a specific non-alcoholic optical screen cleaning solution (Implastec, Brazil) applied with dry microfiber cloths. To prevent cross-contamination, patients are provided with specific disposable ocular masks designed for virtual reality headsets. Furthermore, the head straps are wrapped in a protective plastic film that is replaced between each patient use. Throughout the process, the protocol allows for immediate cessation of the session if any discomfort arises. Moreover, in the unlikely event of a serious or unanticipated adverse reaction, the research team is mandated to halt the intervention immediately, provide appropriate medical care, and report the incident to the Institutional Review Board within 24 h, in compliance with ethical guidelines.

Furthermore, broader secondary clinical trajectories and major postoperative complications are monitored to provide a comprehensive recovery profile. The study tracks the length of stay in both the intensive care unit (ICU) and the hospital, the total cumulative duration of mechanical or noninvasive ventilation required throughout the ICU stay, and the incidence of critical events such as delirium, assessed via the CAM ICU protocol, or paralytic ileus.

Finally, to evaluate the overall hospital experience, patient satisfaction is quantified using the short-form 18-item Patient Satisfaction Questionnaire (PSQ 18) on the fifth postoperative day or prior to hospital discharge. Surpassing the exposure time typically evaluated in previous trials, this protocol delivers a cumulative immersion dose of up to 11.25 h over five days (45 min, three times daily). Consequently, this comprehensive instrument is selected because this sustained and highly immersive acute pain management is hypothesized to generate a robust halo effect. This extensive exposure is theorized to positively alter the patient's global perception of the entire hospital stay, thereby allowing the reliable measurement of core dimensions of care, including technical quality and general satisfaction [22].

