## Standard of care framework

Irrespective of group allocation, all participants receive the institutional standard multimodal anesthesia and analgesia protocol, which is managed by the Acute Pain Service. Intraoperatively, all patients undergo a standardized general anesthesia regimen, including continuous hemodynamic monitoring (5-lead electrocardiogram, pulse oximetry, non-invasive and invasive arterial blood pressure) and controlled mechanical ventilation. Crucially, to provide preventive analgesia and mitigate the neuroendocrine stress response associated with major surgical trauma, early analgesic interventions—incorporating regional techniques such as thoracic epidural placement (T5-T12) or fascial plane blocks, tailored to the specific surgical approach—are systematically performed immediately following anesthetic induction and prior to the surgical incision. Postoperatively, this regimen employs a balanced strategy integrating peripheral analgesics, nonsteroidal anti-inflammatory drugs, and targeted opioid administration. In the immediate postoperative phase, pain is controlled through intravenous morphine titration, consisting of 2 mg boluses administered every 5 to 10 min until a Visual Analogue Scale score below 3 is achieved.

Subsequently, analgesic maintenance is provided via Patient-Controlled Analgesia pumps. These devices utilize a standardized 0.5 mg/ml morphine solution, programmed for demand boluses of 0.5 to 1.0 mg with a 7 to 15 min lockout interval. Furthermore, pain intensity is systematically evaluated as a vital sign during routine hemodynamic checks utilizing the Visual Analogue Scale (VAS). Concurrently, the Richmond Agitation-Sedation Scale (RASS) is monitored by the ICU clinical team as a safety and eligibility parameter. To ensure protocol fidelity and patient safety, a Virtual Reality session is only initiated if the patient is in an optimal state of alertness, defined as a RASS score between −1 (drowsy) and +1 (restless). Patients presenting with severe agitation (RASS ≥ +2) or deep sedation (RASS ≤ −2) will have their sessions postponed until clinical stabilization. Consequently, the uniform application of this baseline framework across all study arms ensures that any variations in cumulative opioid consumption can be attributed directly to the digital interventions being investigated.

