## Statistical analysis plan

The statistical analysis plan will be executed using SPSS software. Initially, continuous variables will be checked for normal distribution using the Shapiro-Wilk test. To compare baseline characteristics and cross-sectional continuous data among the three distinct groups, a One-Way ANOVA or Kruskal-Wallis test will be utilized, as appropriate. Furthermore, categorical baseline outcomes will be assessed through Chi-squared or Fisher's exact tests.

To account for unequal observation windows arising from early hospital discharge or varying ICU lengths of stay, the primary endpoint will be time-standardized. The absolute cumulative opioid consumption will be divided by the individual patient's exact observation time, yielding a standardized rate of Morphine Milligram Equivalents (MME) per 24 h. This primary outcome, along with the longitudinal secondary clinical outcomes (specifically the repeated Visual Analogue Scale scores evaluated at multiple time points), will be analyzed exclusively using Generalized Linear Mixed Models (GLMM). This advanced modeling accounts for intra-subject correlation over time. Crucially, to adjust for the inherent clinical heterogeneity between distinct surgical profiles (e.g., median sternotomy versus thoracic procedures like VATS or Nuss repair), the 'Surgical Type' will be included as a fixed-effect covariate in the model.

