Moreover, the implementation of this protocol relies on a stable technological infrastructure. As identified during pilot assessments, hospital wireless network blind spots can disrupt the delivery of streaming content, necessitating the use of pre-downloaded offline media as a mandatory contingency for the passive therapy arm. Parallel to these technological barriers, language can act as an immersion limiting factor. Since the primary interactive applications utilized, such as First Hand and Oculus First Contact, feature English interfaces and audio, non-fluent patients might experience a reduced sense of presence. The risk of cybersickness, although minimized by the careful selection of appropriate software, also remains a physiological factor that could lead to the premature cessation of sessions in highly susceptible individuals.

Because the protocol strategically focuses on a specific age group of 16 to 40 years to ensure technological familiarity, the results may not be directly generalizable to older populations, who might face completely different cognitive or physical challenges when interacting with VR technology. Ultimately, as a single center trial conducted within a highly specialized academic institution, the findings may have limited external validity when extrapolated to community hospitals with different resource constraints. Furthermore, the study design restricts the evaluation window to the acute perioperative phase, concluding on the fifth postoperative day or at hospital discharge. This timeframe inherently limits the ability to assess the long term impact of the VR intervention on the prevention of chronic postsurgical pain or prolonged opioid dependence.

Finally, as a proof-of-concept trial, this study has inherent statistical limitations. The pragmatic sample size of 20 patients per arm (N = 60 total) is prospectively established without a population-specific a priori power calculation. Consequently, while this sample size is mathematically adequate to detect large clinical effect sizes and provide initial estimates of variance, the study may be underpowered to identify small-to-moderate differences in cumulative opioid consumption or pain intensity. Therefore, the risk of a Type II error cannot be completely ruled out, and these findings should be interpreted as preliminary efficacy signals that require validation in future, fully powered definitive multicenter trials.

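### The primary endpoint, read plainly, counts opioid given before any VR session can start, and the stated model leaves out the intraoperative opioid recorded to adjust for it: the effect is attenuated and precision lost, without bias between arms

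*Protocol article*

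**What the plan says.** **Endpoint.** Under Clinical endpoints and blinding, the protocol article says "The primary clinical endpoint is defined as the cumulative morphine milligram equivalents consumed postoperatively", "which is objectively quantified throughout the entire evaluation period". All administered opioids, rescue doses included, are converted to MME. Limitations gives the end of the evaluation window, "concluding on the fifth postoperative day or at hospital discharge". No section gives its start.

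**When opioid begins.** Standard of care framework: "In the immediate postoperative phase, pain is controlled through intravenous morphine titration". Patient-controlled analgesia follows.

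**When VR begins.** Trial procedures and data collection: "once clinically stabilized after surgery and extubated in the ICU, randomized patients start their assigned VR sessions", on postoperative days one to five. Standard of care framework postpones a session further when the RASS score is out of range.

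**Analysis.** Statistical analysis plan divides each patient's cumulative MME by that patient's observation time to give a rate per 24 h, and analyses it in a mixed model. Surgical Type "will be included as a fixed-effect covariate in the model"; no other covariate is named. Yet Trial procedures and data collection lists bypass duration, anaesthesia time and intraoperative opioid, which "are recorded to account for potential confounding variables in the postoperative analgesic response".

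**The concern.** Opioid given before the first session cannot respond to VR. If it is counted, each patient's outcome is a sum of one part that treatment can change and one part that it cannot. The relative effect shrinks by the share of the second part, whose variation also adds noise. Converting to a rate per 24 h does not help, because the pre-VR hours sit in both numerator and denominator. They weigh most in patients who leave early.

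The model then does not use, as far as the article says, a variable recorded for this very purpose. With 20 patients per arm and adequacy claimed only for large effects, lost precision matters. It also matters beyond this trial, since the stated aim includes giving variance estimates for later definitive trials. An effect and a variance that mix in pre-exposure use would be poor inputs for sizing them.

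**Working it through.** **1. The plan's own figures.** 20 blocks × 3 = 60 = 3 arms × 20, which agrees. No power, standard deviation or MME effect is stated, so there is no power figure to reproduce.

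**2. Inputs that are assumed.** The article gives none of these.
- f: share of total postoperative MME given before the first session, 0.1 to 0.4.
- r: true relative reduction once VR starts, 30%.
- rho: correlation between MME before and after VR starts, 0 to 0.7.
- Equal coefficient of variation in both windows.
- d = 0.8 as a large standardised effect.
- Two-sided 5% test, pairwise, 20 v 20, noncentral t.

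**3. How much time precedes VR.** If counting starts at the end of surgery and the first session comes 12 to 24 h later (assumption), the pre-VR share of observation time is:
- 12/120 to 24/120 = 10% to 20% for a five-day stay;
- 12/72 to 24/72 = 17% to 33% for three days;
- 12/48 to 24/48 = 25% to 50% for two days.

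The MME share would be larger if use is heaviest early.

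**4. Dilution of the relative effect.** Observed reduction = r × (1 − f).
- f = 0.1: 0.30 × 0.9 = 27%
- f = 0.2: 0.30 × 0.8 = 24%
- f = 0.3: 0.30 × 0.7 = 21%
- f = 0.4: 0.30 × 0.6 = 18%

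**5. Dilution of the standardised effect.** With k = f/(1 − f), observed d = 0.8 / √(1 + k² + 2·rho·k). Undiluted power at d = 0.8 is 69%.

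| f | k | d at rho = 0 (power) | d at rho = 0.5 (power) | d at rho = 0.7 (power) |
|---|---|---|---|---|
| 0.1 | 0.111 | 0.795 (69%) | 0.76 (64%) | 0.74 (63%) |
| 0.2 | 0.250 | 0.78 (67%) | 0.70 (58%) | 0.67 (55%) |
| 0.3 | 0.429 | 0.74 (62%) | 0.63 (49%) | 0.60 (46%) |
| 0.4 | 0.667 | 0.67 (54%) | 0.55 (40%) | 0.52 (36%) |

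The loss is negligible in the top left cell and large in the bottom right.

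**6. What adjustment could return.** If MME before the start point is a covariate instead of part of the outcome, residual variance is multiplied by 1 − rho², and the effective d is 0.8/√(1 − rho²).
- rho = 0.4: factor 0.84, d = 0.87, power 77%, equivalent to 60/0.84 = 71 patients
- rho = 0.5: factor 0.75, d = 0.92, power 81%, 60/0.75 = 80 patients
- rho = 0.6: factor 0.64, d = 1.00, power 87%, 60/0.64 = 94 patients

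These gains start from an unadjusted comparison at 69%. Surgical Type is already in the model, so only the correlation that remains after it counts, and the gain would be smaller. For intraoperative opioid the article gives no correlation either.

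**The case against.** The strongest reply is that the window's start is simply not stated. Sessions run from the first postoperative day, so the evaluation period may open then too, and a condensed article may leave this to the full protocol. That stands as a limit: a reader might infer that the early titration is certainly counted, but the article does not settle it. Inclusion is the plain reading of consumption after surgery with all administered opioids converted. Either way, the start of the primary endpoint's window needs stating.

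Second, naming Surgical Type does not say that it is the only covariate, and a fuller plan may list more. That also stands in part. Still, the article has its own statistical analysis section, and that section does not take up the variables recorded to account for confounding.

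Third, total opioid use is a deliberate pragmatic choice, and low power is disclosed. True; this is why whole postoperative MME should be kept, though not as the primary measure of what VR does.

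Two extensions are tempting and are not supported:
- *Ventilation.* The article tracks "the total cumulative duration of mechanical or noninvasive ventilation required throughout the ICU stay". One might infer that most of this precedes VR, but noninvasive support can follow extubation, no figure is given, and it is a descriptive secondary outcome.
- *Regional technique.* One might want it as a covariate, but the article ties the technique to the surgical approach, so Surgical Type probably captures much of it.

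**Conclusion.** The point holds as one of attenuation and lost precision. A reader might infer that the comparison between arms is biased. It is not, on this ground alone: pre-VR opioid enters all three arms alike.

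The relative effect shrinks by the factor (1 − f) whenever f is above zero: 27% to 18% instead of 30% for f of 0.1 to 0.4. The loss in standardised effect runs from 0.80 to 0.795 (f = 0.1, rho = 0) down to 0.80 to 0.52 (f = 0.4, rho = 0.7). All of this rests on assumed f, rho and equal coefficients of variation. The article supplies none, so the size of the loss in this trial is unknown. The gain from adjustment, 69% to about 77% to 87% for rho of 0.4 to 0.6, is an upper guide for the same reason and because Surgical Type may already explain part of it. The plan should be changed, but nothing here invalidates it.

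**What to change.** 1. **Fix the start.** Open the MME numerator and the observation time at one moment that is the same in all three arms and does not depend on care decisions, for example a set clock time on the first postoperative day, when sessions may begin. Extubation with an eligible RASS score is less suitable: it can occur before sessions are allowed and lies in the hands of an unblinded ICU team. Some opioid before a delayed first session will still be counted, equally in all arms.
2. **Keep whole postoperative MME** as a secondary or sensitivity analysis.
3. **Add intraoperative opioid**, already collected, to the model beside Surgical Type. If envelopes are opened before surgery, first confirm that those giving the anaesthetic do not know the allocation; the blinding table does not list them.
4. **MME before the start point.** Make it a covariate in the primary model only if allocation is revealed at or after that point. The article releases the envelope after consent and enrolment without placing this relative to surgery. If allocation is known earlier, this MME is measured after randomisation under an unblinded team, and belongs in a sensitivity analysis only.

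Leave ventilation time and regional technique as they are.

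**Cost.** Wording, plus one or two model parameters. The doses come from the pump logs and records already planned as sources. The counting window becomes shorter, by 10% to 20% of a 120 h stay if 12 to 24 h are removed (assumption).
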